### Recruitment {15}

The recruitment is taking place at the USZ, during evaluations by otorhinolaryngologists. Additionally, there is a website available with the study information, from which interested individuals can learn more about the study and register their interest in trial participation.

## Assignment of interventions: allocation

### Sequence generation {16a}

Specific prognostics may influence the outcomes; therefore, the intervention groups will be balanced to minimize this influence. Randomized group assignment will be performed using pair matching for the two study arms, by way of stratification according to age, sex, hearing loss, and tinnitus severity.

Despite already excluding individuals with slight and catastrophic THI, mean levels in grades 2 to 4 have different impacts among participants [87]. Thus, to obtain this control, participants will be allocated so that both groups will present individuals with the same levels of tinnitus severity.

Randomization will be performed by a software script optimizing group allocation along the defined parameters in a pair-matching manner. The entire study sample will be split in half for the two study arms and random 3-digit strings will be used for all participants.

### Concealment mechanism {16b}

Randomization is performed on pseudonymized study codes with no name or other personal identifiers (i.e., sex, age in years, and tinnitus severity with the THI score).

Randomization is performed by the biometrician who is a researcher independent of the actual study procedures. The allocation list is kept in a separate file on the independent computer, only the biometrician has access to the document.

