#### Other outcome of interest

The other outcomes will be used in order to describe and characterize the study sample, control variables and correlational analyses. These will be assessed only on the second visit, before the first treatment (Fig. 4).

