#### Primary analysis

The data will be statistically analyzed for changes in subjective tinnitus loudness and distress (VAS) and MML by means of frequentist linear mixed-effect modelling (LME) by the biometrician after data collection has been completed.

Between- and within-subjects repeated measures ANOVA will be used to compare the effect of treatment pre and post, in both intervention groups.

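### The two allocation sections disagree on whether hearing loss is a balancing factor, and the primary model does not say how the balancing factors are used

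*Protocol article*

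**What the plan says.** In the protocol article, Sequence generation {16a} says that certain prognostic characteristics may influence the outcomes. It therefore balances the arms "by way of stratification according to age, sex, hearing loss, and tinnitus severity". On method it says: "Randomization will be performed by a software script optimizing group allocation along the defined parameters in a pair-matching manner". It adds: "The entire study sample will be split in half for the two study arms".

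Concealment mechanism {16b} says that randomisation is done on pseudonymised study codes that carry neither a name nor anything else identifying the person, and then gives in brackets: "i.e., sex, age in years, and tinnitus severity with the THI score". Hearing loss is not in that list.

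Intervention description {11a} says that eligibility is checked at the second visit, that the data of an included participant then go to the biometrician for assignment to A or B, and that treatment begins in that same second session. Audiometry is in the second stage of the session and the first stimulation in the third.

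Primary analysis says that the VAS ratings and MML are analysed "by means of frequentist linear mixed-effect modelling (LME) by the biometrician after data collection has been completed", and also: "Between- and within-subjects repeated measures ANOVA will be used to compare the effect of treatment pre and post, in both intervention groups". It lists no model terms. Under Other outcome of interest, the article says: "The other outcomes will be used in order to describe and characterize the study sample, control variables and correlational analyses".

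**The concern.** Two adjoining sections describe the same allocation with different factor lists, and the factor that drops out is the one closest to a primary outcome. MML is the white-noise level needed to cover the tinnitus, so it plausibly depends on hearing. It also sets the level of the acoustic stimulation, which only arm A receives in active form. The eligibility criteria limit hearing loss only up to 2 kHz and limit asymmetry between sides, so loss at higher frequencies may vary considerably between participants.

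Active versus sham is compared within each participant. The added value of acoustic stimulation is compared between participants, A against B, with 20 per arm. An imbalance in hearing between arms bears on that second question.

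If the factors are used to restrict the allocation and then left out of the model, the reported between-arm standard error is also larger than it need be.

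**Working it through.** **The plan's own figure.** Sample size {14} gives 32 participants for a within-between interaction with f = 0.25, alpha = 0.05, 2 groups and 5 measurements. The 0.95 written as beta is read here as power. The article states neither the correlation between measurements nor the sphericity correction; 0.5 and 1 are assumed.

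- Noncentrality = f² × N × m / (1 − ρ) = 0.0625 × 32 × 5 / 0.5 = 20
- Degrees of freedom: (2 − 1)(5 − 1) = 4 and (32 − 2)(5 − 1) = 120
- Power is 0.957 at N = 32 and 0.943 at N = 30, so 32 is the smallest even total.

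The figure reproduces. It shows that the trial is sized on an interaction that includes within-subject change. The target of 40 gives 20 per arm.

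**The two factor lists side by side.**

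| Factor | Sequence generation {16a} | Concealment mechanism {16b} |
|---|---|---|
| Age | yes | named |
| Sex | yes | named |
| Tinnitus severity (THI) | yes | named |
| Hearing loss | yes | not named |

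The list in {16b} can be read in two ways. If it shows what accompanies the codes, hearing loss is missing. If it gives examples of identifiers that the codes do not carry, none of the three reaches the allocation script. Neither reading agrees with {16a}.

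**Chance imbalance if hearing loss is left out.** The between-arm difference in SD units has standard deviation √(2/n).

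- n = 20 per arm: √(2/20) = 0.316; 0.5/0.316 = 1.58; P(|Z| > 1.58) = 0.114
- n = 15 per arm (40 × 0.75 / 2, the stated 25% dropout): √(2/15) = 0.365; 0.5/0.365 = 1.37; P = 0.171

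These are upper bounds, because matching on age, sex and THI also balances whatever part of hearing loss they predict. For illustration, if they explained 30% of its variance (an assumption), then 0.316 × √0.7 = 0.265, 0.5/0.265 = 1.89, and P = 0.059 at 20 per arm.

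**Precision of the between-arm contrast.** Let R² be the share of that contrast's variance explained by the factors. The article gives no value, so 0.1 to 0.3 is assumed. The ratio of unadjusted to adjusted interval width is 1/√(1 − R²). If the factors are balanced but omitted, the actual type I error at a nominal 0.05 is P(|Z| > 1.96/√(1 − R²)).

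| Assumed R² | Width ratio | Actual type I error |
|---|---|---|
| 0.1 | 1.05 | 0.039 |
| 0.2 | 1.12 | 0.028 |
| 0.3 | 1.20 | 0.019 |

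The unadjusted interval is thus 5 to 20% wider. Seen from the other side, at R² = 0.3 the adjusted interval is 1 − √0.7 = 16% narrower. Omission makes the test conservative; it does not bias it.

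**Where R² applies.** For participant i with fixed characteristic x, a main effect γx enters both pre and post, and both the active and the sham block. It cancels from post minus pre and from active minus sham. With complete data, a main-effect covariate therefore leaves the group-by-time estimate and its standard error essentially unchanged. Only a factor that predicts change, entered through an interaction with time or condition or in a model for change, can sharpen that contrast.

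**The case against.** The strongest reply is that {16b} is a sentence about pseudonymisation, not a specification of the allocation record. {16a} still requires hearing loss, and the script works on the parameters defined there. Hearing is an exclusion criterion that must be checked before assignment, so some hearing data should exist by then. This stands as far as it goes. A reader might infer that hearing loss cannot be balanced, but the documents support only that the sections conflict and that balance on hearing loss is not assured.

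A reader might also infer that dividing the whole sample in half is impossible when participants are allocated during recruitment from April 2021 to December 2022. The sentence may mean no more than a 1:1 ratio, and matching of participants as they enrol is feasible. What remains is that the text does not describe it.

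A third tempting reading is that the primary analysis ignores the balancing factors. The article names no model terms at all, which is not exclusion. It mentions control variables elsewhere, and a condensed article may leave model terms to the full protocol or analysis plan. The absence of a covariate list is therefore not an error in itself.

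Finally, the precision figures rest on an assumed R² and on a between-arm contrast, whereas the trial is sized on an interaction. That is correct, and it limits both the claim and the form that any adjustment should take.

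**Conclusion.** The contradiction between the two allocation sections is real, is not resolved elsewhere in the article, and should be removed. Its possible consequence is moderate: up to an 11% chance of a hearing imbalance above 0.5 SD with 20 per arm (up to 17% with 15). This holds only if allocation actually runs on the shorter list, and the chance is lower to the extent that hearing loss follows the matched factors. Such an imbalance would be a chance event, not a systematic bias. That hearing affects MML is a plausible assumption, in line with the article's own choice of hearing loss as a balancing factor.

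On the analysis, the supported conclusion is narrower: no use of the balancing factors is tied to the primary model, and stating one would be worthwhile. The benefit for the A versus B comparison depends on how well the factors predict the outcome or its change. For active versus sham within participants it is small.

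**What to change.** 1. Give the same four factors in Sequence generation and Concealment mechanism. Reword the parenthesis in the latter so that it says plainly which variables accompany the study code.
2. Add a defined hearing-loss measure to the record sent to the biometrician, derived from the pure tone audiometry already collected. The article defines no summary, so the ears and frequencies to be averaged must be stated. Because audiometry and first treatment fall in the same session, also state that the value is available before allocation.
3. Replace the sentence on halving the sample with a description of 1:1 matched allocation of participants as they enrol.
4. In the primary mixed model, include the balancing factors for the between-arm comparison in a form that can affect it: factor-by-time or factor-by-condition terms, or a baseline-adjusted model for change. Main effects alone would do little.

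The cost is one more column in the allocation record, a few sentences and no new measurement. In the analysis, four single-degree terms in a two-arm model for change reduce the residual degrees of freedom from 40 − 2 = 38 to 34, or from 30 − 2 = 28 to 24 with 30 completers. A baseline term takes one more.

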### Implementation {16c}

The enrollment of participants is performed by two professionals who are not participating in laboratory procedures. The allocation sequence and the assignment of participants to interventions will always be performed by the biometrician who also is never part of any treatment visits or procedures.

## Assignment of interventions: Blinding

### Who will be blinded {17a}

Participants and researchers performing the treatments and measurements will be blinded. The information about the course of the training is kept identical for participants in both groups: the position of the electrodes is the same, and the duration of stimulations and sessions are the same for both groups. In addition, the current in the sham condition is applied during the first and last 30 s of stimulation as a ramp up and ramp down, respectively, thus the participant feels a tingling sensation similar to the active stimulation. TRNS and AS is programmed in such a way that the study personnel are blinded to the active or sham status of these interventions.

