### Trial design {8}

The study is a double-blind, pseudo-randomized (stratified randomization), sham-controlled, crossover within- and between-subject design with two study arms (i.e., testing 2 protocols vs. sham).

Overall, participants will undergo 20 stimulation visits and 6 additional assessment visits (Fig. 1).

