## Interventions

### Explanation for the choice of comparators {6b}

The study intervention consists of a bilateral HD-tRNS application over temporal regions, parallel to the application of AS in one study arm. Stimulus intensity will be below individual sensation threshold, with a max. of 2 mA. AS will never surpass 85 dB SPL at the ears.

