#### Study intervention(s) group B = control intervention

HD-tRNS bilateral temporal regions for 20 minSham HD-tRNS bilateral temporal regions for 20 min

Sham conditions are planned for both study arms to test the interventions with respect to placebo effects. The standardized sham HD-tRNS protocol of the DC-Stimulator will ramp up to 2 mA current for 30 s before ramping down to 0 mA to elicit the sensation of a faint tingling on the scalp to imitate the sensation of active tES. The AS sham condition is purposely constructed to present very low sound energy. The tES sham protocol is standard and thus best practice in basic and clinical research whereas the Sham AS is novel in its conception and use (i.e., no specific references available).

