#### Acoustic stimulation (AS)

For acoustic stimulation, WN with an intensity of MML + 10 dB is used. The AS is also applied for 20 min and will never surpass 85 dB SPL at the ears.

For Sham AS, deep pure tones at SL + 10 dB are used, varying randomly between [1] 100 and 200 Hz [2], 1.33 and 4 Hz presentation rate [3], randomly varying in intensity ± 10% around the SL + 10 dB level, and [4] randomly varying linear decay envelope between 250 and 750 ms. The AS sham condition is purposely constructed not to cover the tinnitus pitch range and to present very low sound energy, so as not to be able to generate tinnitus suppression. The randomization of frequency, temporal, and intensity parameters ensures the absence of any regularities (including musical properties).

The AS is performed using Etymotic ER-2 research-grade, air conduction in-ear headphones (Etymotic Research Ins., USA), as with these it is possible to get quasi-linear response in frequencies up to 14 kHz compared to other air tube headphones. The intention behind the use of these headphones for AS and the auditory paradigm is to optimize the transmission of the acoustic signals and the absence of ferromagnetic metal in respect to not interfere the EEG measurements or tES being provided at the same time.

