### Minimum masking level (MML)

The MML measures the level of sound needed to cover the perception of tinnitus. It is adjusted to the lowest level of noise (white noise—WN) until tinnitus is thoroughly masked, in a diotic presentation [65, 69].

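### The trial is called double-blind, but the measures described do not secure participant blinding for arm A active versus sham or for arm A versus arm B, and the descriptions of active and sham current conflict

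*Protocol article*

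**What the plan says.** All references are to the protocol article.

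- **Blinding claim.** Trial design {8} calls the study a "double-blind, pseudo-randomized (stratified randomization), sham-controlled, crossover within- and between-subject design". Who will be blinded {17a} says "Participants and researchers performing the treatments and measurements will be blinded". The Discussion relies on the double-blinded crossover to compare HD-tRNS and bimodal stimulation with sham.
- **Measures behind the claim.** Section {17a} lists the same information for both groups, the same electrode positions, the same durations, a sham current that tingles, and programming that hides active or sham status from personnel.
- **Arms.** Under Study intervention(s) group A, active current is paired with acoustic stimulation (AS) and sham current with sham AS. Under group B, active or sham current is listed with no sound.
- **Sounds.** Under Acoustic stimulation (AS), "For acoustic stimulation, WN with an intensity of MML + 10 dB is used". Under Minimum masking level (MML), white noise is adjusted "until tinnitus is thoroughly masked". Sham AS is a varying series of 100–200 Hz tones 10 dB above sensation level, chosen to avoid the tinnitus pitch range and any suppression.
- **Active current.** Explanation for the choice of comparators {6b}: "Stimulus intensity will be below individual sensation threshold, with a max. of 2 mA".
- **Sham current.** Under group B, the sham protocol "will ramp up to 2 mA current for 30 s before ramping down to 0 mA", so that a faint tingling imitates active stimulation. In {17a}, "the current in the sham condition is applied during the first and last 30 s of stimulation", with a tingling said to be like that of active stimulation.
- **Primary outcomes {12}.** Visual analog scale (VAS) loudness, VAS distress and MML.

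**The concern.** The primary objective is about combined electric and acoustic stimulation. It is served by two comparisons: active versus sham within arm A, and arm A versus arm B. In both, the conditions differ in something the participant can plainly hear, and the blinding section deals only with the electric component.

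The outcomes are exposed to this. Two are the participant's own ratings, and the third depends on the participant saying when the tinnitus is covered. If participants work out which block is real, or that they are in the arm with the fuller treatment, expectation can move all three without any bimodal effect. A positive result would then be hard to attribute. The conflicting accounts of the current raise a separate doubt, which reaches the active-versus-sham contrast in both arms.

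**Working it through.** The plan states no figure on this point, so the check sets the sections side by side.

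**Step 1: arm A, active versus sham block.**

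| | Active block | Sham block |
|---|---|---|
| Current | active | sham |
| Sound | white noise, MML + 10 dB | 100–200 Hz tones, sensation level + 10 dB |
| Tinnitus during sound | covered, since MML already masks it fully | not covered, by design |

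Every arm A participant experiences both columns. The sounds differ in spectrum, in level and in whether the tinnitus stays audible. Sound and current status always change together, so recognising the sound reveals the current. There is a further cue: the residual inhibition test also uses white noise at MML + 10 dB, and the tinnitometry battery is scheduled before the first treatment. Participants have therefore met that signal before treatment starts.

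**Step 2: arm A versus arm B.** Arm A has a sound in every treatment session and arm B has none listed. Equal electrode positions, durations and information do not remove an audible difference. The programming statement covers active or sham status, not arm.

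**Step 3: is active current felt?** Section {6b} puts it below the individual sensation threshold. The group B section and {17a} justify the sham tingling by its likeness to active stimulation. As written, these do not agree.

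**Step 4: when is sham current on?** The group B section describes one ramp up followed by a return to 0 mA. Section {17a} describes current in the first and last 30 s. These are different schedules.

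**Step 5: the listed amplitudes (HD-tRNS section).**

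- TP7, T8, T7: 0.69 + 0.78 + 0.53 = 2.00 mA.
- Other 14 channels: 0.05 + 0.17 + 0.15 + 0.06 + 0.22 + 0.16 + 0.18 + 0.25 + 0.05 + 0.07 + 0.20 + 0.10 + 0.21 + 0.12 = 1.99 mA.

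This fits a 2 mA total, so the conflict concerns perceptibility and sham timing, not the maximum. The section does not say how these amplitudes relate to an individual sensation threshold.

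**Step 6: what a bias could do (illustration only).** Assume no true effect, a simple two-arm comparison at two-sided 0.05, and an expectation bias of b standard deviations between arms. With n per arm, SE = √(2/n), and the false-positive rate is Φ(b/SE − 1.96) + Φ(−b/SE − 1.96). For n = 20 and b = 0.3: SE = 0.316, b/SE = 0.949, and the rate is 0.156 + 0.002 = 0.158.

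| Assumed b | n = 16 per arm | n = 20 per arm |
|---|---|---|
| 0 | 5.0% | 5.0% |
| 0.2 | 8.7% | 9.7% |
| 0.3 | 13.6% | 15.8% |
| 0.5 | 29.3% | 35.3% |

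The values of b are assumptions. Nothing in the document says which applies, if any.

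**The case against.** The strongest reply is that hearing a difference is not the same as knowing what it means. Sham AS is an audible placebo, not silence. Both groups receive the same information, and the participant information is not shown. An arm B participant who hears nothing learns the arm only if told that others hear something. This stands as a limit: a reader might infer that blinding fails, but the document supports only that it is not secured. It does not answer arm A, where each person compares the two sounds directly.

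A reader might also infer that staff can tell the arms apart. That is not supported. Sound is delivered through in-ear headphones, the article does not say whether arm B wears silent ones, and personnel are stated to be blind to active or sham status. Questionnaires are answered without the evaluator present, which limits staff influence on the VAS ratings.

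Two readings of the current go too far. One is that sham is the condition that is felt. Active stimulation also ramps up and down, so this does not simply follow. The other is that the montage is a fixed 2 mA. Both {6b} and the targeting description treat 2 mA as an upper limit, so the list may show the montage at that limit.

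Finally, the Discussion attaches the double-blind claim to comparisons with sham and treats arm A versus arm B separately. It also admits that there is no sound-only branch. That is fair, but arm A active versus sham is a comparison with sham, and blinding is not among the stated limitations. A condensed article may leave a guess item to the full protocol. It cannot leave its own contradictory statements there.

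**Conclusion.** The concern holds in limited form. Participant blinding is not secured by the described measures for arm A active versus sham or for arm A versus arm B, and the statements on active and sham current contradict each other in perceptibility and in sham timing. All three primary outcomes rest on participant report or judgement, so expectation could contribute to either bimodal comparison. Its direction and size cannot be derived from the document.

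It would be tempting to conclude that group B's active-versus-sham contrast is safely blinded, since no sound is involved. The document does not support that yet, because the unresolved conflict over the current affects group B as well.

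The conclusion assumes that masking-level white noise and faint low tones are distinguishable to the listener, which follows from how the protocol defines them. It also assumes that no undescribed measure, such as silent earphones or particular wording to participants, closes the gap between arms.

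**What to change.** 1. Reconcile the statements on current in {6b}, the group B section, the HD-tRNS section and {17a}: whether active stimulation is meant to be felt, how the listed amplitudes relate to the individual threshold, and when sham current is on. No setting is proposed here.
2. In Trial design {8}, {17a} and the Discussion, state that participant blinding is not secured for arm A active versus sham or for arm A versus arm B. Claim it for group B active versus sham only once item 1 is settled.
3. At the end of each block, add to the existing post-session safety questionnaire one item asking which condition the participant thinks was given, with a certainty rating. Report the answers descriptively by arm and block. Do not split the primary contrasts by guess: the guess is made after treatment and may reflect whether the tinnitus improved, so conditioning on it can itself introduce bias.

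The cost is some rewording, one extra item per block (two per participant) and a weaker blinding claim. Allocation, sample size and primary analysis are unchanged.
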